### 2.3. Sample size

Considering that the focus of omics studies is the mechanism of the intervention effect, the sample size estimation of our exploratory research is distinctive compared with classical randomized control trials. Given previous literature regarding the omics analysis of acupuncture (44–46), at least 15 participants in each group are required. Thus, we set at least 15 participants in each group in the present design. Allowing for a 20% dropout rate, we plan to recruit 40 participants (20 participants per group).

#### 2.3.1. Recruitment strategies

Participants were enrolled between April 2022 and March 2023. The current study utilized two primary resources to identify and recruit potential subjects: advertisements, including printed media such as roll-up banners and social media such as WeChat, and patients recommended by doctors. No registration fee was charged, and acupuncture treatments and scale assessments were provided free of charge. The flow of the trial is presented in Figure 1. The schedule of enrollment, interventions, and assessment, as well as visits for participants during the trial, is shown in Figure 2.

**Figure 1 F1:**
[figure not shown]
Flow diagram.

**Figure 2 F2:**
[figure not shown]
Schedule of trial enrollment, interventions, and assessments.

### 2.4. Intervention

To ensure the optimal effects of acupuncture stimulation, all treatments were performed by one certified acupuncturist with more than 3 years of experience in practice. Before the trial, special training regarding the process and standard operation of the treatment will be provided.

#### 2.4.1. Qihuang needle therapy

The QH needle is divided into four parts as follows: the tip, the shaft, the handle, and the protective cap (Figure 3). Its tip is flat-bottomed, circular, and three-edged, ensuring safety and reducing stabbing pain at the moment of penetration (47). The needle body is a hollow tube with higher strength and toughness compared with common filiform needles. Its transparent and anti-slip handle facilitates the observation of hemorrhages, and the protective cap is made of disposable material that is non-toxic.

**Figure 3 F3:**
[figure not shown]
Qihuang needle **(left)** and the protective cap **(right)**.

Based on the meridian sinew theory and clinical experience, Baihui (GV20), Yintang (EX-HN3), and Jueyinshu (BL14) will be selected as the main acupoints. Xiyangguan (GB33), Fuliu (KI7), Danzhong (CV17), and Qihaishu (BL24) are additional acupoints. KI7 will be chosen for patients with leg twitches, and CV17 will be used where vocal tic disorders occur. BL24 is for waist movement disorder. BL14, GB33, KI7, and BL24 will be stimulated bilaterally. The acupuncture points are described in Table 2 and presented in Figure 4.

**Table 2 T2:** Framework of the acupuncture point prescription.

**Acupuncture points**	**Description**
GV20: Baihui (p213)	On the head, 5B-cun superior to the anterior hairline, on the anterior median line
EX-HN3: Yintang	On the head, between the right medial end of the eyebrow and the left one
BL14: Jueyinshu (p116)	In the upper back region, at the same level as the inferior border of the spinous process of the fourth thoracic vertebra (T4), 1.5 B-cun lateral to the posterior median line
GB33: Xiyangguan (p188)	On the lateral aspect of the knee, in the depression between the biceps femoris tendon and the iliotibial band, posterior and proximal to the lateral epicondyle of the femur
KI 7: Fuliu (p139)	On the posteromedial aspect of the leg, anterior to the calcaneal tendon, 2 B-cun superior to the prominence of the medial malleolus
CV17: Danzhong (p228)	On the anterior medial line of the chest, at the midpoint between the two nipples, at the level of the fourth intercostal space
BL24: Qihaishu (p111)	In the lumbar region, at the same level as the inferior border of the spinous process of the third lumbar vertebra (L3), 1.5 B-cun lateral to the posterior median line.

The prescribed acupoints come from the WHO Standard Acupuncture Point Locations in the Western Pacific Region.

**Figure 4 F4:**
[figure not shown]
Location of acupoints.

We aim to apply QH needles (patent no. ZL2015 20271867.0; 0.3 × 0.13 × 30 mm; QH; Chongqing Figure 3) in the acupuncture treatment. Manipulation (48) will be done as follows. After skin disinfection, the QH needles will be inserted vertically into the myofascial. Then, the needle will be directed toward the diseased site, and its handle will be gently moved from side to side at an angle of 15–30. When the “de qi” sensation (feelings of numbness, tingling, swelling, soreness, or muscle weakness) becomes obvious (~10 s after stimulation), the needle will be withdrawn. The pinholes will be pressed with a sterile, dry cotton ball without needle retention. As for the Baihui acupoint, the needle will be inserted perpendicularly into the galea aponeurotica, then withdrawn slightly, and the abovementioned manipulation will be performed. As for the Yintang acupoint, the needle will be inserted obliquely into the subcutaneous, and the abovementioned manipulation will be performed.

Participants in the experimental group will receive eight sessions of acupuncture treatment (two times a week for 4 weeks), and participants in the healthy control group will not receive the intervention.

### 2.5. Outcome evaluations

The clinical evaluations include the assessment of the severity of tics and gastrointestinal symptoms. The recurrence rate will be measured after a 12-week follow-up. The primary outcome measure will be the Yale Global Tic Severity Scale (YGTSS), and secondary outcomes will consist of the gastrointestinal severity index (GSI) and the recurrence rate. Biological specimen analysis outcomes will include changes in the composition of intestinal microbiota, serum metabolites, and serum zonulin. YGTSS and GSI will be assessed at baseline and after 4 weeks when the interventions have been completed. Data relating to the recurrence rate will be collected after a 12-week follow-up. Feces and serum samples will be collected at baseline and 4 weeks after the interventions. If sample collection is concurrent with a treatment, sample collection will be performed after all interventions have been completed. The feces sample will be collected as soon as possible after completing all interventions.

#### 2.5.1. Primary outcomes

##### 2.5.1.1. Change in YGTSS score

The YGTSS is the most widely used rating scale for tic assessment, both in clinical practice and research. It has the best evidence in the assessment of tic severity and indicates acceptable psychometric quality (49, 50). An experienced pediatric clinician carries out the YGTSS by asking the parents or guardians of the participants to answer the questions and by observing participant performance during visits to the clinic. The total score (maximum rating of 100) is the sum of the scores of motor and vocal tics and functional impairment. A YGTSS score < 25 indicates mild severity; 25–50, moderate; >50, severe.

#### 2.5.2. Secondary outcomes

##### 2.5.2.1. Change in GSI

The GSI, applied in the present study to rate the gastrointestinal signs and symptoms, was originally used in a 2006 study by Schneider et al. (51). This 9-item GSI rating scale was used to assess gastrointestinal symptoms in children with tic disorders, and its correlation with the gut microbiome was investigated (25). The rating scale consists of nine gastrointestinal signs and symptoms (constipation, diarrhea, average stool consistency, stool smell, flatulence, abdominal pain, unexplained daytime irritability, nighttime awakening, and abdominal tenderness), and the total possible severity score is 17, with a higher score corresponding to greater severity.

##### 2.5.2.2. Recurrence rate

The rate of recurrence will be calculated as the number of recurrences divided by the number of participant return visits.

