**Expected outcomes:**

The change in the severity of the tic disorder is set as the main outcome. Secondary outcomes include gastrointestinal severity index and recurrence rate, which will be calculated after a 12-week follow-up. Gut microbiota, measured by 16S rRNA gene sequencing; serum metabolomics, assessed *via* LC/MS; and serum zonulin, assessed by enzyme-linked immunosorbent assay (ELISA), will be used as biological specimen analysis outcomes. The present study will investigate the possible interactions between intestinal flora and serum metabolites and the improvement of clinical profiles, which may elucidate the mechanism of Qihuang needle therapy for tic disorders.

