In addition, to improve the clinical practice of acupuncture, we will further construct a prediction model based on multi-omics data and clinical profiles. Considering the small sample size, we will attempt to use the transfer learning method to develop a prediction model for personalized acupuncture treatment. Transfer learning is used to transfer knowledge from a generalized model to a more domain-specific model. It would enable the utilization of biological data published in the literature and reduce the demand for data collection when investigating new processes. Rogers et al. (55) showed that transfer learning is a highly data-efficient technique to predict the modeling of bioprocesses, a typically low-dimensional, small-data problem, but its usage in the biomedical field is scarce. In the present study, we will extract generalizable knowledge from well-understood published biological data, capturing essential process mechanisms to set a source model. We will then apply this understanding to characterize and screen novel samples and refine the model with our data. Our study is a new attempt to develop a prediction model for personalized acupuncture treatment.

Because most participants enrolled are school-aged children, they may have class during normal working hours, which may affect timely treatment. Therefore, we will make an appointment with parents after enrollment and keep in touch with them every week during the treatment sessions. In addition, we will do a 6-month follow-up to reduce the number of patients lost to follow-up. We will also maintain contact with the parents *via* WeChat or telephone and follow up through these channels.

This study has some limitations. There have been no acknowledged biomarkers for the assessment of tic severity. The rating of YGTSS is based on clinical experience in working with patients with tic disorder and their families, which is probably subjective. The sample size is small, and the follow-up duration is not very long.

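### The recurrence rate is divided by return visits instead of by children who had improved, so it understates the risk of recurrence

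*Protocol article*

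**What the plan says.** Section 2.5.2.2 of the protocol article gives the whole definition in one sentence: "The rate of recurrence will be calculated as the number of recurrences divided by the number of participant return visits". It does not restrict the denominator to children whose tics had improved.

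The timing of this outcome is stated three times, always as 12 weeks: in the abstract ("recurrence rate, which will be calculated after a 12-week follow-up") and twice in section 2.5 ("The recurrence rate will be measured after a 12-week follow-up" and "Data relating to the recurrence rate will be collected after a 12-week follow-up").

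Section 2.5 also says "YGTSS and GSI will be assessed at baseline and after 4 weeks when the interventions have been completed". Week 4 is therefore the point at which improvement on the primary scale is known.

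The Discussion, in a paragraph on scheduling and keeping contact with parents, says "we will do a 6-month follow-up to reduce the number of patients lost to follow-up". It does not tie that period to the recurrence rate.

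**The concern.** A recurrence needs a prior improvement. The children at risk are those who had improved when treatment ended, and a recurrence rate should describe them. The formula uses a different base in two respects.

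- **Who is counted.** Children who returned without having improved add to the denominator and can never add to the numerator.
- **What is counted.** The denominator is visits and the numerator is recurrences. Neither is a count of children, so the result is a proportion of children only when each child contributes one visit and at most one recurrence.

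This is the only listed outcome that speaks to whether benefit lasts. A reader will take it as the chance that an improved child relapses. The formula gives a lower number than that, and how much lower depends on how many children failed to improve, which is not a property of relapse at all.

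**Working it through.** **Figures in the plan.** No recurrence rate is assumed or predicted anywhere, so there is no recurrence figure to reproduce. The related design figure is the group size. Section 2.3 states that "at least 15 participants in each group are required" and allows 20% dropout: 15/(1 − 0.20) = 18.75, rounded up to 19. The plan recruits 20 per group, and 20 × 0.80 = 16 children remain. That figure is in order, and 16 is used below as the number returning.

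**Notation.** n = children returning, R = those among them who had improved at week 4, p = risk of recurrence among improvers, v = return visits per child. Each child is taken to have at most one counted recurrence.

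- Expected recurrences: p × R
- Rate as the plan defines it: (p × R)/(n × v)
- Rate among children able to recur: (p × R)/R = p
- Ratio of the first rate to the second: R/(n × v)

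The two agree only if v = 1 and R = n, that is, one visit each and every returning child improved.

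**One visit per child**, the reading closest to section 2.5. Assumptions: n = 16, p = 50%.

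| Improvers R | Recurrences | Plan's rate | Risk among improvers |
|---|---|---|---|
| 8 | 4 | 4/16 = 25% | 4/8 = 50% |
| 12 | 6 | 6/16 = 37.5% | 6/12 = 50% |
| 16 | 8 | 8/16 = 50% | 8/16 = 50% |

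The risk is the same in all three rows. The plan's rate doubles from the first to the last only because more children improved.

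**One reported figure, two different situations.** With 8 improvers of whom 4 relapse, the plan reports 4/16 = 25%. With 4 improvers who all relapse, it also reports 4/16 = 25%. The risks among improvers are 50% and 100%.

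**More than one visit per child** (conditional, since no text shown plans it). With R = 8 and p = 50%, two visits each give 4/32 = 12.5% and three give 4/48 = 8.3%.

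**Precision.** The exact (Clopper–Pearson) 95% interval, from beta quantiles, is 15.7% to 84.3% for 4/8 and 7.3% to 52.4% for 4/16. The narrower interval belongs to the wrong quantity.

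**The case against.** The strongest reply is that the phrase is a loose rendering of participants who returned. Section 2.5 describes one collection of recurrence data after 12 weeks, so visits and returning children would be the same number. That is a fair reading, and it makes the visit-count effect conditional: no text shown plans several follow-up visits, and the schedule in Figure 2 is not shown. It does not remove the inclusion of children who had not improved, which is the whole of the error in the one-visit table.

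A second reply is that this is an exploratory trial with about 20 treated children. Healthy controls have no tics to recur, section 3.1.1 names no test specifically for recurrence, and nothing else in the plan depends on it. This stands and limits the severity.

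Four stronger readings might be inferred, and the document does not support them.

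- **Two time points for the outcome.** Every statement tied to recurrence says 12 weeks. The 6 months in the Discussion concerns general follow-up and retention.
- **A less effective treatment always reports a lower rate.** This holds at a fixed risk among improvers, but not in general. Going from 8 improvers at 50% to 4 at 100% leaves the reported rate at 25%; 10 improvers who all relapse would give 10/16 = 62.5%.
- **No tic score exists at follow-up.** Section 2.5 lists the YGTSS only at baseline and week 4, but the unshown Figure 2 may list more. A condensed article may also leave the working definition of recurrence to the full protocol.
- **The figure cannot be compared with any other study.** That would need sources that are not at hand.

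**Conclusion.** The point holds for the denominator. The plan states a formula that, followed as written, does not give the risk of recurrence among children able to recur. With one visit per child it understates that risk by the factor R/n, which is one half if 8 of 16 returning children had improved (25% against 50%) and three quarters if 12 had (37.5% against 50%). There is no understatement if every returning child improved. The counts and the 50% risk are assumptions, since the document gives neither. The direction rests on at least one returning child not having improved and on each child's recurrence being counted once.

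The difference between 12 weeks and 6 months is a separate, smaller inconsistency in the length of follow-up, not in the timing of this outcome.

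Severity is moderate: this is a descriptive secondary outcome, and the primary YGTSS analysis, the omics analyses and the sample size are unaffected.

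**What to change.** Replace the sentence in section 2.5.2.2 with a definition per child at risk:

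- **Numerator:** children among the improvers with at least one recurrence by the 12-week follow-up.
- **Denominator:** children who met a YGTSS improvement threshold at week 4, the threshold being fixed before the data are seen.
- **Reporting:** both counts, an exact 95% confidence interval, and the number of improvers not followed up, so that the reader can see how much rests on those who returned.

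Separately, reconcile the 6-month follow-up in the Discussion with the 12 weeks in the abstract and section 2.5, and say what, if anything, is collected at each.

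The cost is a change of wording, because the week 4 YGTSS is already scheduled. The downside is a smaller denominator and a wider interval, as the 4/8 example shows. A repeat YGTSS at the 12-week follow-up would make recurrence score-based, but it is not required for this correction. It may already be in Figure 2. If it is not, it could need a clinic visit, because section 2.5.1.1 bases the scale partly on observing the child and the Discussion plans follow-up by WeChat or telephone.

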### 2.2. Eligibility criteria

Participants must fulfill the diagnostic criteria for provisional tic disorder and persistent motor or vocal tic disorder according to the DSM-5 (2). Patients will be screened according to the inclusion and exclusion criteria listed in Table 1.

**Table 1 T1:** Eligibility criteria.

	**TD patients**	**Healthy controls**
Inclusion Criteria	1. Aged between 4 and 18 years	1. Matched age, sex, family history of a psychiatric condition, parental marital status, mode of delivery and birth weight to the TD group^*^
	2. Meeting the diagnostic criteria of transient tic disorder and Persistent Motor or Vocal Tic Disorder according to the Diagnostic and Statistical Manual of Mental Disorders, Fifth Edition (DSM-5) (1, 2)	2. No current or history of head trauma, convulsions, epilepsy, growth and development disorders, mental illness, digestive system disease, abdominal operation or asphyxia at birth
	3. The course of a provisional tic disorder is more than 3 months	3. No current or history of medication of mental disorders especially drug influencing neurotransmitters
	4. The score of YGTSS >12	4. The mother is healthy during pregnancy (no history of infection, digestive system disease, trauma or taking any medication)
	5. Have not received acupuncture or moxibustion within 3 months, and drug withdrawal period ≥12 weeks	
	6. Guardians are willing to sign the informed consents	
Exclusion Criteria	1. Secondary tic disorders	
	2. Patients with severe diseases of important organ systems: liver and kidney damage, cardiovascular insufficiency, metabolic diseases, malignant tumors, etc., which may adversely affect our clinical observation	
	3. Obsessive-compulsive disorder, depression, Attention deficit hyperactivity disorder, anxiety, autism spectrum disorder, eating disorder, or a history of substance abuse	
	4. Epilepsy, Huntington's disease, rheumatic chorea, hepatolenticular degeneration, substantia nigra degeneration, psychogenic tics and other extrapyramidal disorders	
	5. The use of antibiotics, probiotics, high-dose vitamin or immunomodulatory medications within 4 weeks before the fecal sample collection	
	6. Conditions like any infective diseases or other severe disorders that may influence the gut microbiota	
	7. Ulcers or surgical scars on the acupoint area	
	8. Children who are participating or participated in other clinical trials within 1 month	

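### The recurrence rate is taken over return visits, not over children who had improved, so it mixes response with durability

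*Protocol article*

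**What the plan says.** Section 2.5 of the protocol article gives the outcome its status: "secondary outcomes will consist of the gastrointestinal severity index (GSI) and the recurrence rate". Section 2.5.2.2 then fixes the calculation, and it is the only definition in the document: "The rate of recurrence will be calculated as the number of recurrences divided by the number of participant return visits".

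Four other statements bear on it:

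- Timing, section 2.5: "Data relating to the recurrence rate will be collected after a 12-week follow-up".
- Follow-up length, section 5 (Discussion): "we will do a 6-month follow-up to reduce the number of patients lost to follow-up".
- Tic ratings, section 2.5: "YGTSS and GSI will be assessed at baseline and after 4 weeks when the interventions have been completed".
- Entry severity, Table 1 in section 2.2: "The score of YGTSS >12".

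The article states neither what counts as a recurrence nor what improvement must come before one.

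**The concern.** Every treated child enters with tics above a severity threshold. In the ordinary sense of the word, a recurrence needs an earlier improvement: a child whose tics never eased has nothing to recur. The stated denominator nevertheless takes in the return visits of all treated children, improved or not. Non-improvers add to the denominator and can add nothing to the numerator.

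The rate is presumably meant to describe how long the benefit of the needle therapy lasts. As defined, it falls when fewer children respond, even if the improvers relapse just as often. There is no second treated group to set it against, so a reader will take the number at face value. The Discussion also lists lower recurrence among the benefits reported for acupuncture, which invites that reading.

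The unit is a further problem. Recurrences over visits is a proportion of children only if each child has exactly one visit and can contribute at most one recurrence.

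**Working it through.** **Inputs from the protocol article.** The formula (2.5.2.2); at least 15 per group, a 20% dropout allowance and 20 recruited per group (2.3); data collection after 12 weeks (2.5) and a 6-month follow-up (5). No response rate or recurrence rate is given, so every rate below is an assumption.

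**The plan's own figure.** The article gives no recurrence figure to reproduce. Its sample size does reproduce: 15 / 0.8 = 18.75, rounded up to 19, against 20 stated. With 20% lost, 20 × 0.8 = 16 treated children remain, which meets the minimum of 15. About 16 children is therefore the realistic size of the follow-up set.

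**Algebra.** Let n children return, with m visits each. Let r be the share improved by week 4 and q the share of improvers who relapse, counted once per child.

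- Rate as defined: (n·r·q) / (n·m) = r·q/m
- Rate among improvers: (n·r·q) / (n·r) = q

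**One visit per child (m = 1), assumed q = 40%.**

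| Share improved | Rate as defined | Rate among improvers |
|---|---|---|
| 90% | 0.9 × 0.4 = 36% | 40% |
| 70% | 0.7 × 0.4 = 28% | 40% |
| 50% | 0.5 × 0.4 = 20% | 40% |

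**A second assumed relapse share.** With q = 30% and 20 children returning, 80% response gives 4.8/20 = 24% and 40% response gives 2.4/20 = 12%. Among improvers both are 30% (4.8/16 and 2.4/8).

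**When relapse also differs.** Start from 80% response with 30% relapse, which the formula reports as 24%. A treatment with 40% response reports the same 24% once its relapse share reaches 60% (0.4 × 0.6). At 70% relapse it reports 28% (0.4 × 0.7). The direction therefore depends on relapse among improvers being equal, or not so much higher that it offsets the lower response.

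**More than one visit.** With q = 30% and two visits per child, 24% and 12% become 12% and 6%. With three visits they become 8% and 4%. The children and the recurrences are unchanged.

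**Can the visit count be settled?** Section 2.5 points to one collection time, after 12 weeks of follow-up. The Discussion speaks of 6 months. Counting from baseline does not reconcile them: 4 weeks of treatment plus 12 weeks is 16 weeks, and 6 months is about 26. Figure 2 holds the visit schedule but was not available for this check.

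**The case against.** The outcome is secondary and the article calls the research exploratory. Only one group is treated, healthy controls cannot have a tic recurrence, and section 3.1.1 names no test specific to recurrence. Change in YGTSS is reported for the same children, so weak efficacy would be visible beside the rate. All of this stands, and it limits the severity.

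It can also be said that a condensed article may leave the meaning of recurrence to a fuller protocol. That excuses the missing definition but not the formula, which is stated outright and has the wrong denominator under the ordinary meaning of the word. Reading return visits as children who returned does not rescue it, because non-improvers are still counted.

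Three stronger readings are tempting, and the document does not support them:

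- **A weaker treatment always shows a lower recurrence rate.** This holds only with relapse among improvers held equal. With one treated group, no ranking of treatments within the trial can be distorted.
- **Children are counted more than once.** Section 2.5 gives a single collection time, and with one visit and at most one recurrence per child the figure is a proportion of returning children. Repeated counting is only a possibility that the 6-month remark leaves open.
- **A relapse reported by phone enters the numerator while that child is missing from the denominator.** The Discussion does say that contact is kept by "WeChat or telephone and follow up through these channels", but the article does not define a return visit, and nothing says that such contacts are excluded from the count.

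**Conclusion.** The point holds in a limited form. The denominator of the recurrence rate is not restricted to children who had improved, so the figure is the product of response and relapse rather than a measure of durability. Across assumed response shares from 90% down to 50%, a constant 40% relapse among improvers is reported as anything from 36% to 20%.

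This rests on two assumptions: recurrence means return of tics after improvement, and each child has one return visit. If there is more than one visit per child, the ratio also ceases to be a proportion of children and shrinks with the number of visits.

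The consequence is a descriptive secondary rate that cannot be interpreted as written. The primary outcome, the sample size and the omics analyses do not depend on it. It should be fixed before the results are reported; it is not critical to the trial.

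**What to change.** Rewrite section 2.5.2.2 so that each child is counted once:

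- **Denominator:** treated children who met a pre-stated YGTSS improvement criterion at week 4 and were assessed at the follow-up time.
- **Numerator:** those children with at least one recurrence, under a pre-stated definition assessed in the same way for every child.
- **Reported alongside:** the number of non-improvers, the number of children not assessed, and an exact binomial 95% confidence interval.
- **Follow-up length:** the 12-week statement in section 2.5 and the 6-month statement in section 5 must be reconciled, so that the follow-up time has one meaning.

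Both criteria should be set before the follow-up data are examined.

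Identifying improvers needs no new data, since the week-4 YGTSS is already planned. A uniform assessment of recurrence may need more: the text lists YGTSS only at baseline and week 4, so the follow-up assessment has to be specified. The statistical cost is a smaller denominator, a wider interval and usually a higher reported rate. Precision is low in any case: 4 recurrences among 16 children would give 25%, with an exact 95% interval of 7% to 52%, and restricting to improvers leaves 16 or fewer if 20% drop out.
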